#### Sensitivity analyses for the primary outcome

Sensitivity analyses will be performed to assess the impact of areas of uncertainty surrounding the primary outcome analysis and its robustness. The data within centres may be correlated, and a regression analysis appropriate for the data distributions and model assumptions will be conducted, which will allow for this clustering in order to obtain an unbiased estimation of the treatment effect and its standard error (SE). Other factors that could threaten the robustness of results might be (1) how the outcome is defined, i.e. if time management skills is expressed as a continuous or a dichotomous variable; (2) number of sessions attended in the LGO-S; and (3) differences in characteristics between participants lost to follow-up and those staying in the trial. Analyses related to point 2 above will involve conducting a per-protocol analysis in which individuals having participated in 7 or more sessions are regarded as “programme completers” (i.e. as having complied with the protocol sufficiently).

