#### The “Let’s Get Organized” group intervention

LGO-S is a 16-week group intervention with weekly 1.5-h sessions and is divided into two parts. Part 1 (10 sessions) is focused on time management, and part 2 (6 sessions) is focused on organising and planning activities [57]. In this trial, only part 1 will be evaluated. Each group has six to eight participants and is led by two trained group leaders. The key mechanisms in the LGO-S intervention are goal-directed and other learning strategies, which are used to train effective time management habits such as maintaining a calendar and wearing a watch. The LGO-S material is comprised of a course manual for the leaders with accompanying PowerPoint presentations and working material for each session. White [49] (p 713) asserts that group sessions follow the same structure with specific stages, “to ensure integration and generalisation of new learning and establish proper habit formation”. Each group session has a set theme, which is different for each session (Table 1), and six stages that are common to all ten sessions:

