#### Individual occupational therapy (TAU)

The control intervention will be TAU, which is individual occupational therapy services targeting time management, organisation, and planning. This intervention involves both individual coaching and training, as well as prescriptions of time-assistive products. Sweden’s National Board of Health and Welfare’s mandatory web education called “The Prescription Process” guides the process of product selection, when necessary adaptations are made, information, education and training, follow-up, and evaluation [60]. The TAU intervention does not necessarily standardise the number of visits or the duration of the programme. Rather, each intervention is individually tailored. Thus, the OTs are instructed to perform the intervention as they would usually do, which includes one or more visits for assessments followed by advice regarding structuring of activities in daily life, devising schedules or other low-tech aids for time management, prescription or advice on time-assistive devices, and conducting training in how to use time-assistive devices in daily life. The TAU in this trial will be limited to 10 weeks.

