#### Trial-specific forms

Two trial-specific demographic forms will be collected only at pre-intervention. One form will be filled out by the participant with their information, including age, sex, family status, living arrangements, and information on education and work. The second form will be filled out by the recruiting staff and contains information on diagnosis, medication, length of contact with the services, and any prior prescribed time-assistive devices and contacts with an occupational therapist. In the case of dropouts, the time of occurrence will be noted, along with the reason if given by the participant.

To evaluate the process of implementing the interventions, a form will be filled out for each participant by the interventionist. For participants receiving the LGO-S intervention, the form will document the number of sessions, as well as which sessions they attended. For participants receiving TAU, the form will document the number of sessions, the time duration per session, the content of any interventions, and prescribed and/or recommended cognitive assistive devices.

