### Statistical analysis plan

#### General statistical considerations

The flow of participants through the study will be illustrated according to the Consolidation Standard of Reporting Trials (CONSORT, Fig. 1) [78].

Prior to data analysis, raw data from each instrument will be coded according to the instructions for the respective instrument. Statistical tests will be two-sided and conducted at the conventional (two-sided) 5% level with no formal adjustment for multiple testing. Secondary outcomes are likely to be highly correlated so that standard adjustment techniques, such as the Bonferroni method, would be conservative [79].

All outcome measures and patient characteristics will be summarised by their trial allocation group and by measurement point. The distribution of outcome data will be examined. The main analysis of outcome data will be the comparison of change from baseline between treatment arms. Change from baseline has a “normalising” effect and standard techniques are generally applicable. To maintain the baseline comparability of the compared groups, the main analyses will be performed on an intention-to-treat basis, meaning that participants will be analysed in the arm they were allocated to. A researcher blinded to group allocation will conduct the statistical analysis, guided by a professional academic statistician (also blinded).

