## Methods: monitoring

### Data monitoring

Staff that are providing intervention and collecting parts of the data have been trained in giving the LGO-S intervention by the Swedish Association of Occupational Therapists. To maintain adherence to the trial protocol, interventionists will be gathered for network meetings four times a year, and this will be complemented with visits to the units by the researchers. There is a risk that participants will discontinue treatment or be partially absent from treatment in either treatment arm due to e.g. lack of motivation, lack of time, worsened health or meeting, and travel restrictions due to the COVID-19 pandemic. All deviations from the protocol will be noted by the interventionists. Interim analyses will be performed when 50% of the participants have completed their last assessment. The data collection will stop when the stipulated number of participants is reached or when the principal investigator makes such a decision based on interim analyses. The principal investigator will have the final decision regarding the termination of the trial. No stopping guidelines have been deemed necessary because there are no, or very minor, risks with participation. The extended research group (the authors of this protocol, and in addition two other colleagues) functions as a steering committee that the PI and the project coordinator will report to on a regular basis and also discuss issues with arising during the trial.

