### Ancillary and post-trial care

Participants who are allocated to TAU will be offered to participate in the LGO-S intervention after completing all assessments in this trial. Likewise, individual TAU will be offered to participants in the LGO-S intervention. Participants will be monitored for psychological well-being throughout the trial by the interventionists. If needed, psychological support from the treating unit will be offered to the participant.

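### The per-protocol sensitivity analysis defines completers by LGO-S attendance alone, so it gives up the randomised comparison and may be biased, plausibly but not certainly towards LGO-S

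*Protocol article*

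**What the plan says.** All places are in the protocol article.

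- *Sensitivity analyses for the primary outcome* names "number of sessions attended in the LGO-S" as one factor that could threaten the robustness of the result. The response is "conducting a per-protocol analysis in which individuals having participated in 7 or more sessions are regarded as" having complied sufficiently with the protocol.
- *The “Let’s Get Organized” group intervention* gives the denominator: "Part 1 (10 sessions) is focused on time management". Only this part is evaluated, so the rule means 7 of 10.
- *Individual occupational therapy (TAU)*: "The TAU intervention does not necessarily standardise the number of visits or the duration of the programme". No completion rule for TAU is given.
- *Trial-specific forms*: LGO-S attendance is recorded session by session. TAU contact is recorded too: "For participants receiving TAU, the form will document the number of sessions, the time duration per session".
- *General statistical considerations*: "the main analyses will be performed on an intention-to-treat basis, meaning that participants will be analysed in the arm they were allocated to".
- *Ancillary and post-trial care* sets when the control arm gets access to LGO-S: "Participants who are allocated to TAU will be offered to participate in the LGO-S intervention after completing all assessments in this trial".

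The protocol does not say outright which TAU participants enter the per-protocol comparison.

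**The concern.** Attendance is observed after randomisation. If it goes with the outcome for reasons other than the treatment, restricting one arm to good attenders makes the arms differ even when LGO-S adds nothing over TAU. *Data monitoring* expects absence through "lack of motivation, lack of time, worsened health or meeting, and travel restrictions due to the COVID-19 pandemic". Motivation and health could plausibly go with self-rated change. Lack of time and travel limits need not.

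What is at stake is interpretation. The analysis is offered as a check on robustness. If it errs in the hypothesised direction, it gives false reassurance beside a positive intention-to-treat result, or an apparent rescue beside a null one. If it errs the other way, it casts doubt on a sound result. In neither case does it isolate the effect of attending LGO-S.

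**Working it through.** **Inputs from the protocol.** SD 10, target difference 8 ATMS units, 25% dropout and 52 per arm (*Sample size*); two-sided 5% tests (*General statistical considerations*). A two-sample t-test with difference 8, SD 10, two-sided alpha 0.01 and 80% power needs 39 per arm; 39 / (1 - 0.25) = 52 per arm, 104 in total. The plan's figure is reproduced and is not affected by this point.

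**Inputs not in the protocol, so assumed.** p is the share of LGO-S participants reaching 7 sessions. r is the correlation between the propensity to attend and the change in ATMS-S.

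**1. Bias under no effect, LGO-S completers against all of TAU.** Let completers be those with normal attendance propensity above c, where c is the (1 - p) quantile. Then bias = SD × r × φ(c) / p.

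| p | φ(c)/p | r = -0.3 | r = 0 | r = 0.2 | r = 0.3 | r = 0.5 |
|---|---|---|---|---|---|---|
| 60% | 0.644 | -1.93 | 0 | 1.29 | 1.93 | 3.22 |
| 75% | 0.424 | -1.27 | 0 | 0.85 | 1.27 | 2.12 |
| 90% | 0.195 | -0.58 | 0 | 0.39 | 0.58 | 0.97 |

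Units are ATMS units; positive favours LGO-S. Example: 10 × 0.3 × 0.424 = 1.27.

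**2. False-positive rate in favour of LGO-S** (nominal 2.5%; simulated with 52 per arm and no dropout, 8,000 runs per cell). For r = 0.2, 0.3 and 0.5:

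- p = 60%: 8.4%, 13.6%, 29.4%
- p = 75%: 6.0%, 8.7%, 16.9%
- p = 90%: 3.6%, 5.3%, 7.5%

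At r = 0 the rate is 2.3% to 2.5%. At r = -0.3 the excess rejections go against LGO-S: total two-sided rejection is 13.4% at p = 60% and 8.8% at p = 75%.

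**3. If dropout follows the same propensity in both arms.** Suppose the 25% with the lowest propensity leave each arm, 70% of randomised LGO-S participants complete, and r = 0.3. LGO-S completers then have mean 10 × 0.3 × 0.497 = 1.49. The remaining 75% of TAU have mean 10 × 0.3 × 0.424 = 1.27. The bias is 1.49 - 1.27 = 0.22 units, so most of it cancels.

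**4. The complier-average estimate.** TAU participants are offered LGO-S only after all assessments, so non-compliance is one-sided by design and the estimate is the intention-to-treat difference divided by p. In the same simulations under no effect it averaged within 0.1 unit of zero in every scenario. Its SD was about 3.3, 2.6 and 2.2 units at p = 60%, 75% and 90%.

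**5. Where that estimate fails.** It assumes that people attending fewer than 7 sessions gain nothing over TAU. If completers gain 8 and partial attenders gain e, it returns (8p + e(1 - p)) / p. With e = 4:

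- p = 60%: (4.8 + 1.6) / 0.60 = 10.7
- p = 75%: (6.0 + 1.0) / 0.75 = 9.3
- p = 90%: (7.2 + 0.4) / 0.90 = 8.4

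If partial attenders do worse than they would have done under TAU, e is negative and the estimate falls below 8.

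**The case against.** The strongest reply has four parts.

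*The comparator is inferred.* The protocol does not say that all of TAU is used. TAU sessions are recorded, and a TAU rule may stand in an analysis plan that is not shown. This is fair, and the absence of such a rule is not itself the finding. But TAU is individually tailored, so a visit count would select on something different, such as need or complexity. A TAU rule could shrink the bias or change its sign; it would not restore the randomised comparison.

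*The direction is not established.* A reader might infer that the analysis favours LGO-S whatever the truth. The documents do not support that. The outcome is change, not level, and better-organised attenders may have less room to improve. Some listed reasons for absence need not be prognostic. The bias is nil at r = 0 and negative when r is negative.

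*The size rests on unsourced inputs.* This stands. People lost to follow-up are probably often low attenders too, so completion among those analysed may be high and the bias small (step 3).

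*The alternative has its own bias.* A reader might also infer that the complier-average estimate should simply replace the per-protocol analysis. That goes too far. The first six sessions already cover appointment books, activity schedules, time estimation and prioritising, so no effect below 7 sessions is doubtful. The overstatement in step 5 is 2.7 units at p = 60% and 1.3 at p = 75%, comparable with the per-protocol bias. Adding the estimate is justified; dropping the conventional analysis is a preference.

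**Conclusion.** The point holds as a low-severity one. The completer rule is tied to LGO-S attendance and has no TAU equivalent, so the per-protocol contrast selects after randomisation in a way that cannot be matched across arms. Under no effect the bias lies between about -1.9 and +3.2 ATMS units over the assumed ranges (p 60% to 90%, r -0.3 to 0.5). A bias towards LGO-S is plausible because motivation and health are among the expected reasons for absence, but it is not certain. These figures assume that all of TAU is the comparator and that attendance propensity and change are jointly normal with SD 10. Neither p nor r is given in the protocol. The primary conclusion is protected, since the main analysis is intention-to-treat and nothing in the protocol lets the per-protocol result override it.

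**What to change.** Amend the sensitivity-analysis text as follows.

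1. State which TAU participants enter the 7-session comparison. Label it descriptive and do not use it as evidence of robustness.
2. Add a complier-average causal effect estimate: two-stage least squares with randomised arm as the instrument for attending 7 or more sessions, adjusted for baseline ATMS-S and centre.
3. Add a version with number of LGO-S sessions attended as the exposure.
4. State the assumptions. The first estimate needs no effect over TAU below 7 sessions; the second needs a linear effect per session. Both need outcome data from low attenders, or principled handling of their missing data.

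The cost is a few sentences and a few lines of code. Session counts are already collected. The price is a wider confidence interval and assumptions that the data cannot fully check, so the added estimates should be read beside the intention-to-treat result and not in its place.

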#### Secondary outcome analysis

Secondary outcomes will be analysed according to the same procedure as the primary outcome analysis. If applicable, a secondary analysis for best responders in the trial will be conducted by pooling the two treatment arms and applying a suitable regression model.

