## Methods: participants, interventions, and outcomes

### Objectives

The aim of this trial is to evaluate the effectiveness of the LGO-S intervention in open psychiatric or habilitation care to improve time management for adults with impaired time management skills due to mental or neurodevelopmental disorders.

In comparison to treatment as usual (TAU, namely individual occupational therapy), we hypothesise that LGO-S is:
More effective in improving self-assessed time management skills, regulation of emotions, satisfaction with daily occupations, occupational balance, and self-efficacyEqually effective in improving self-assessed organisation and planning skills, aspects of executive functioning, and psychiatric symptomsMore effective in improving parental sense of competence for parents with children living at homeA cost-effective method to increase the individual’s quality of life and self-reported time management skills

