### Sample size

A total of 104 participants will be recruited for the trial. There will be 52 participants in each group. The sample size calculation is based on the earlier feasibility study showing that an increase of 8 ATMS units in mean difference (SD = 10 for both groups) on the time management subscale of the ATMS-S was considered a significant effect [52]. Furthermore, the calculation took into account an 80% power to detect change, a dropout rate of 25%, and a statistical significance level of *p* < 0.01.

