#### Primary outcome analysis

The pre-specified primary endpoint in this trial is the change from baseline in time management skills as measured with the ATMS-S immediately after the intervention compared between the LGO-S and TAU treatment arms. Differences will be analysed with an independent *t*-test or the Mann–Whitney *U*-test, depending on the distribution.

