## Discussion

As shown in the literature review, difficulties with time management are frequently reported in people with diagnoses such as mental or neurodevelopmental disorders. The consequences of such difficulties for these people and for society as a whole speak for a need for methods to overcome these difficulties. There are, to our knowledge, currently no documented evidence-based interventions aiming to improve time management and organisational skills in adults with mental or neurodevelopmental disorders. The trial described in this paper will create new evidence for the efficacy of the LGO-S intervention, which is designed to target time management skills. The earlier results from the feasibility study of the LGO-S are promising and warrant the need for a randomised trial, which will provide robust evidence regarding its efficiency and whether there are any improvements beyond those of TAU. The qualitative study of participants in LGO-S suggested that the group setting format further enhances the experience of self-efficacy after the intervention, but whether this is true or not remains to be seen in this trial.

The results of the trial will inform us further on the possible benefits of LGO-S compared to TAU in improving self-assessed time management skills, regulation of emotions, satisfaction with daily occupations, occupational balance, and self-efficacy. It will also increase our understanding as to whether LGO-S is equally efficient as TAU at improving self-assessed organisation and planning skills, improving aspects of executive functioning, and improving psychiatric symptoms. Furthermore, this trial will add knowledge about whether LGO-S is more efficient than TAU in improving parental sense of competence for parents with children living at home. Finally, the trial will demonstrate whether LGO-S is a cost-effective way to target time management skills in the clinical setting.

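### Three secondary domains carry a hypothesis of equal effectiveness, but the only planned analysis is a difference test, which can contradict equality and cannot support it

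*Protocol article*

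**What the plan says.** The Objectives section of the protocol article separates two kinds of comparative hypothesis. LGO-S is expected to be more effective than TAU on time management, regulation of emotions, satisfaction with daily occupations, occupational balance and self-efficacy, and on parental competence among parents with children at home. It is expected to be equally effective in "improving self-assessed organisation and planning skills, aspects of executive functioning" and psychiatric symptoms. The Discussion returns to this and says the trial will add to understanding of "whether LGO-S is equally efficient as TAU at improving self-assessed organisation and planning skills, improving aspects of executive functioning, and improving psychiatric symptoms".

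The analysis sections make no such separation. Under Secondary outcome analysis: "Secondary outcomes will be analysed according to the same procedure as the primary outcome analysis". Under Primary outcome analysis: "Differences will be analysed with an independent *t*-test or the Mann–Whitney *U*-test, depending on the distribution". Under General statistical considerations: "Statistical tests will be two-sided and conducted at the conventional (two-sided) 5% level with no formal adjustment for multiple testing".

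The Sample size section is built on "an increase of 8 ATMS units in mean difference (SD = 10 for both groups) on the time management subscale", with 80% power, 25% dropout and a significance level of 0.01, giving 52 per arm. The article states no equivalence or non-inferiority margin, no confidence-interval criterion and no rule for interpreting a non-significant secondary result.

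**The concern.** One procedure is assigned to two opposite kinds of hypothesis. For the outcomes where superiority is expected, a significant difference test supports the hypothesis. For the three domains where equality is expected, the same test can only count against it. A non-significant result shows that the data did not exclude zero. It does not show that the difference is small, and it becomes more likely as the trial gets smaller or noisier.

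With neither a margin nor an interval criterion, the planned analysis has no legitimate route to a positive answer on this hypothesis. What is at stake is false reassurance: a group programme could be described as matching individual occupational therapy on organisation, executive functioning and symptoms when the trial was too imprecise to tell.

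**Working it through.** **Step 1: reproduce the sample size.** Inputs from the Sample size section: difference 8, SD 10, power 0.80, significance level 0.01 (taken as two-sided), dropout 25%. The noncentral t calculation gives 39 evaluable per arm (power 81.0%). Then 39 / (1 − 0.25) = 52 per arm, or 104 in total, as stated. The number is sound for what it was designed to do, which is to detect a difference on the time management subscale.

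**Step 2: inputs for organisation and planning.**
- Number analysed per arm: 39 (52 less 25%) up to 52 (no loss).
- SD of change: 10. This is an assumption. The article gives it for the time management subscale only, although both subscales are expressed in 0–100 ATMS units.
- Test: two-sided 5%, from General statistical considerations.

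**Step 3: precision.** SE = SD × √(2/n), and the 95% half-width = t(0.975, 2n − 2) × SE.
- n = 39: SE = 10 × √(2/39) = 2.26; half-width 4.51 units.
- n = 52: SE = 10 × √(2/52) = 1.96; half-width 3.89 units.

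These are 4.51/8 = 56% and 3.89/8 = 49% of the 8-unit design difference. The half-width scales with the SD. If the SD were 8, it would be 4.51 × 0.8 = 3.6 to 3.89 × 0.8 = 3.1 units. If the SD were 12, it would be 4.51 × 1.2 = 5.4 to 3.89 × 1.2 = 4.7 units.

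**Step 4: probability of a non-significant result when a real difference exists.** This is 1 minus the power of the t-test, from the noncentral t distribution with noncentrality (true gap)/SE.

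| True gap (units) | 39 per arm | 52 per arm |
|---|---|---|
| 3 | 74% | 67% |
| 4 | 59% | 48% |
| 5 | 41% | 29% |

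A true gap of 4 units, half the design difference, would be non-significant about half the time or more.

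**Step 5: what an equivalence test could deliver at this size.** The article gives no margin, so those below are illustrative. Two one-sided tests at 5% each declare equivalence when the 90% CI lies inside the margin. Power by simulation, with a true difference of 0 and SD 10:

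| Margin (units) | 39 per arm | 52 per arm |
|---|---|---|
| 5 | 41% | 63% |
| 6 | 67% | 84% |
| 8 | 94% | 98% |

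Check by normal approximation for margin 5 and n = 39: 2Φ(5/2.265 − 1.665) − 1 = 0.41.

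With 39 per arm, of the margins shown only the 8-unit one, equal to the design difference itself, exceeds 80% power.

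No comparable figures in raw units can be given for the WCPA-SE outcomes or the symptom scales, because the article states no SD for them.

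**The case against.** A reader might infer that the protocol plans to treat non-significance as proof of equality. It does not say so. The Secondary outcome analysis section names a procedure and gives no rule of interpretation, so the misreading is a risk and not a stated plan.

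A reader might also infer that the hypothesis cannot be addressed at all. That goes too far: a significant difference on any of these outcomes would contradict it. Only support for equality is out of reach.

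A milder reading of the hypothesis is plausible. The description of LGO-S says that its second part covers organising and planning and that only the first part is evaluated here. For that domain, equal effectiveness may mean no more than that superiority is not expected. The Discussion is also cautious and speaks of increased understanding, not proof. If that is what is meant, the defect is mainly one of wording, which favours the simpler remedy.

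The figures have limits that stand. They cover one of three domains, borrow an SD from another subscale, and depend on how many participants are analysed. Intention-to-treat analysis with full information maximum likelihood, which the missing-data section allows, could bring precision closer to the 52-per-arm end of the range.

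That a separate analysis plan may exist does not remove the point. The article itself fixes the test for these outcomes, and that test does not fit the hypothesis it is meant to serve.

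**Conclusion.** The mismatch stands. A hypothesis of equal effectiveness on three secondary domains is paired only with a test for a difference, and nothing in the article would allow a positive conclusion. The size of the risk is known only by illustration: for organisation and planning, at an assumed SD of 10 and with 39 to 52 per arm, true gaps of 3 to 5 units would go undetected between 74% and 29% of the time.

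This should be fixed, but it does not threaten the trial's main result. The outcomes are secondary, and neither the primary endpoint, its test nor the sample size is affected.

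**What to change.** In the Objectives and the Discussion, replace the equal-effectiveness wording for all three domains with estimating the between-arm difference with a 95% CI. Under Secondary outcome analysis, add that a non-significant p-value will not be reported as equality.

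If an equality claim is to be kept for any outcome, fix and justify an equivalence or non-inferiority margin for it. The deadline matters. The trial is open, 75 of 104 participants had been recruited by April 2021, and interim analyses are planned when half have completed their last assessment. The margin should therefore be set before anyone sees outcome data by arm, interim results included. Claim equivalence only if the 90% CI lies within the margin, or non-inferiority only if the one-sided 97.5% limit does. Report a per-protocol analysis alongside; at present one is planned only for the primary outcome.

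The cost is a few sentences, plus a justified margin for each claim retained. No extra participants or data are needed to reword. The downside is that some equality claims may end as inconclusive, which is likely for margins well below 8 units if about 39 per arm are analysed.
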